Accurate diagnosis of PMR/GCA can be challenging since various diseases mimic these conditions and there are no specific diagnostic tests. PMR is a clinical diagnosis. Careful clinical evaluation and exclusion of several mimics of PMR/GCA can support the diagnosis.^[1–3]^ In cases of suspected GCA, temporal artery biopsy (TAB) should be performed to confirm the diagnosis. However, it is invasive, it can be false-negative in a proportion of patients, and it does not delineate the extracranial component of the disease.^[7,8]^ Laboratory findings are nonspecific in PMR/GCA. Marked elevations in erythrocyte sedimentation rate (ESR) and C-reactive protein (CRP) are frequently seen in PMR/GCA. Thrombocytosis, anemia, and increased alkaline phosphatase may also be presented.^[1,3]^ Different imaging modalities, for example, ultrasonography (US), magnetic resonance imaging, and angiography, are helpful in the diagnosis of PMR/GCA; however, use of these modalities may be limited due to long assessment time for wide vascular assessment, interobserver variation, invasiveness, diminished sensitivity, specificity, and so on.^[9–11]^ There have been several proposed diagnostic criteria for PMR.^[12–15]^ The core components included in these diagnostic criteria were as follows: an age cut-off point, bilateral shoulder or hip pain, morning stiffness, elevated ESR, elevated CRP, rapid steroid response, and disease duration. In 2012, the provisional classification criteria for PMR has been published by European League Against Rheumatism (EULAR) and American College of Rheumatology (ACR).^[10]^ However, it is worth mentioning that these are classification criteria and are designed to differentiate PMR from other diseases that mimic PMR and are not useful to make the diagnosis. Furthermore, the specificity of the 2012 provisional classification criteria for PMR seems to be not sufficient, despite high sensitivity.^[16]^

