### Secondary

2.2

1.To investigate the validity of 18F-FDG PET/CT scan for diagnosis of PMR/GCA compared with temporal artery biopsy.2.To compare the efficacy of nationally recommended conventional diagnostic workup to detect occult malignancies in the setting of PMR/GCA (ie, chest X-ray [CXR] plus abdominal US) with 18F-FDG PET/CT at diagnosis and during the first year after diagnosis.3.To evaluate the influence of inflammation on regional and total bone mineral density (BMD) and body composition, and also vasculitis/arterial stiffness of aorta at diagnosis of PMR and within a year after treatment initiation with prednisolone.

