#### Study II: evaluating validity of 18F-FDG PET/CT scan for diagnosis of polymyalgia rheumatica and giant cell arteritis compared to temporal artery biopsy: an agreement study

3.4.2

Recent literature is in favor of the ability of 18F-FDG PET/CT scan to detect vasculitis at an early stage, which is important to decide on treatment plan.^[32]^ However, the superiority of 18F-FDG PET/CT scan in comparison with TAB is still arguable. This study will compare 18F-FDG PET/CT scan to TAB. As mentioned in the study I, all included patients will undergo an 18F-FDG PET/CT scan. In addition to 18F-FDG PET/CT scan, TAB will be performed before or within 1 week of steroid treatment initiation. TAB will be taken by experienced otolaryngologist at Department of Ear, Nose and Throat, Svendborg Hospital. The results of biopsy will be compared with the 18F-FDG PET/CT findings after 1 year, when the 18F-FDG PET/CT results are revealed and compared with regards to the degree of agreement between the 2 modalities.^[33,34]^

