### Outcomes

3.8

The primary outcome measure are as follows:1.To evaluate the cumulated prednisolone doses, VAS, patients’ assessment of pain, morning stiffness, VAS for physician evaluation, biochemistry results, that is, ESR, CRP, and fibrinogen, and the eventual number of relapses at baseline and during the first year after treatment initiation (weeks 12, 24, 36, and 48) in patients with PET-positive and PET-negative as described above.

The secondary outcome measures are as follows:1.To elucidate the degree of agreement between PET positivity (vasculitis in the large vessels, and also findings compatible with PMR) and TAB positivity.2.To elucidate the degree of agreement between PET negativity (no signs of vasculitis in the large vessels) and TAB negativity.3.To reveal the prevalence of malignancies in the patients detected by the aim of 18F-FDG PET/CT scan and subsequently compare to the prevalence of malignancies detected by the aim of CXR plus abdominal US.4.To reveal the prevalence of malignancies in the patients detected by the aim of CXR plus abdominal US and subsequently compare to the prevalence of malignancies detected by the aim of 18F-FDG PET/CT scan.5.To evaluate BMI, T score, Z score, LBM, FM, BMD, BMC, FFM, FFMI, and FMI at baseline and after 1 year of treatment initiation.6.To evaluate aortic PWV, upper limb PWV, and aortic augmentation index of included patients at baseline and during treatment (weeks 12, 24, 36, and 48).

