### Statistical analysis

3.12

It is anticipated that 80 participants are likely to be included during a period of 1 year. The results will be considered as significant if *P* value <0.05. Statistical analysis has been discussed below with respect to each individual study.

In study I, data will be descriptive (mean ± standard deviation). Comparisons of the data, between the PET-positive and PET-negative patients, will be made with the Mann–Whitney *U* test or Student *t* test, depending on whether or not the distribution is normal. When comparing 2 binary variables, the chi-square test will be performed. Correlation analysis will be performed with Pearson correlation test.

Study II consists of descriptive statistics and proportions of agreement.

Study III consists of descriptive statistics. Comparisons between groups will be made with McNemar test. The sample size of 80 patients is sufficient to indicate a difference of 15% in detection rate of malignancies with 18F-FDG PET-CT scan as opposed to CXR plus abdominal UL (with a significance level of 5% (1-sided), power of 80%, and assuming discordant proportions of 15% and 0%).^[52]^

Study IV consists of descriptive statistics. Univariate comparisons between groups will be made with the Mann–Whitney *U* test or Student *t* test, depending on whether or not the distribution is normal. When comparing 2 binary variables, the chi-square test will be performed. Analysis of repeated measurements over time will be done by means of mixed linear models, using standard errors that allow for intragroup correlation, relaxing the usual requirement that the observations be independent. Comparison of the above mentioned baseline data, matched by age and sex, will be made, to the extent that these data are available.

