## Discussion

4

The proposed study will explore the potential role of 18F-FDG PET/CT scan in the early diagnosis and management of PMR/GCA before initiation of steroid treatment, and also the association between 18F-FDG PET/CT findings and the clinical picture of the patients. Though 18F-FDG PET/CT is not yet capable of evaluating temporal artery due to inadequate resolution, the extracranial involvement of large vessels, mainly thoracic aorta, carotid, and subclavian, can be delineated.^[53]^ Patients with positive 18F-FDG PET/CT findings will be classified as having GCA and not isolated PMR, which is of great importance in the clinic due to different steroid treatment regimes. Besides, GCA patients with aortic involvement are at increased risk of aneurysm formation, who seek close monitoring.^[54]^ It is our hope that our results elucidate the 3 main areas of concern regarding the management of PMR/GCA including: malignancy, osteoporosis/changes in body composition, the vasculitis process, and the interaction between them, and ultimately elucidate factors predictive of the disease outcome.

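### Study II defines PET-positive and PET-negative so that they overlap, and agreement with temporal artery biopsy cannot by itself establish the stated validity

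*Protocol article*

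**What the plan says.** The secondary objective (section 2.2) reads "To investigate the validity of 18F-FDG PET/CT scan for diagnosis of PMR/GCA compared with temporal artery biopsy". Section 3.4.2 says the two results will be "compared with regards to the degree of agreement between the 2 modalities", and section 3.12 adds only that "Study II consists of descriptive statistics and proportions of agreement".

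Section 3.8 lists two separate outcomes for this comparison:
- Secondary outcome 1: "degree of agreement between PET positivity (vasculitis in the large vessels, and also findings compatible with PMR) and TAB positivity".
- Secondary outcome 2: "degree of agreement between PET negativity (no signs of vasculitis in the large vessels) and TAB negativity".

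Other sections also bear on what PET-positive means. Section 3.4.1 lists a PET-negative group without large-vessel vasculitis and a PET-positive group with PMR-type findings. Section 3.4.1.1 sets positivity at a visual score of 2 or more on an arterial scale, over six arterial compartments that do not include the temporal artery. The Discussion says patients with a positive scan will be classified as GCA, not isolated PMR.

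On the limits of the two tests, the Discussion says "Though 18F-FDG PET/CT is not yet capable of evaluating temporal artery due to inadequate resolution", and the Introduction says of TAB that "it can be false-negative in a proportion of patients, and it does not delineate the extracranial component of the disease". The Introduction also describes PMR as a clinical diagnosis.

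**The concern.** There are two linked problems.

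The first is definitional. Positive and negative agreement should come from one 2×2 table in which every patient is either PET-positive or PET-negative. In section 3.8 the positive category includes PMR uptake, but the negative category ignores it. The same patient can then enter both outcomes with opposite labels, and the two proportions do not describe one classification.

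The second is the step from agreement to validity. TAB samples an artery that PET cannot evaluate, and PET surveys arteries that TAB does not sample. TAB is also not a test for PMR, although the validity aim covers PMR. A discordant pair may therefore mean that both tests are right about different vessels.

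At stake is the conclusion of a secondary objective. Section 3.13 hopes that TAB may not be needed in future, while allowing that a small number of patients may still require it.

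**Working it through.** The plan states no expected agreement, precision or sample size for Study II, so there is no figure to reproduce. Step 1 needs only the definitions. Steps 2 to 4 are illustrations under assumed rates.

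**Step 1. Definitions side by side.** Outcome 1 is read here as PET-positive when either finding is present.

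| PET finding | Outcome 1 label | Outcome 2 label |
|---|---|---|
| Vasculitis, with or without PMR uptake | positive | not negative |
| PMR uptake only | positive | negative |
| Neither | not positive | negative |

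Only the middle row is inconsistent. If TAB is negative, that patient disagrees in outcome 1 and agrees in outcome 2. If TAB is positive, the reverse holds. Section 3.4.1 has the same overlap. The Discussion would classify this patient as GCA if the positive label is used.

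**Step 2. How many patients could carry both labels.** Assume 80 patients (the planned number): 60 with PMR only, 12 with cranial GCA and 8 with large-vessel GCA. Assume PMR uptake in every PMR-only patient and in half of cranial GCA, vasculitis on PET in every large-vessel GCA patient and in no other, and no reading errors.
- PET-positive under outcome 1: 60 + 6 + 8 = 74.
- PET-negative under outcome 2: 60 + 12 = 72.
- In both: 74 + 72 − 80 = 66.

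If only half of the PMR-only patients show uptake, the overlap is 30 + 6 = 36.

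**Step 3. Effect of the definition, with the same error-free scans.** Assume TAB positive in 80% of cranial GCA, 50% of large-vessel GCA and 0% of PMR only. Cells are expected counts.

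Vasculitis only as PET-positive:
- both positive 4; PET+/TAB− 4; PET−/TAB+ 12 × 0.8 = 9.6; both negative 60 + 2.4 = 62.4
- overall agreement (4 + 62.4)/80 = 83%, so 17% are discordant without any reading error
- positive agreement 2 × 4/(2 × 4 + 13.6) = 37%
- negative agreement 2 × 62.4/(2 × 62.4 + 13.6) = 90%
- kappa 0.28

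PMR uptake also counted as PET-positive:
- both positive 6 × 0.8 + 4 = 8.8; both negative 6 × 0.2 = 1.2
- overall agreement (8.8 + 1.2)/80 = 12.5%
- with uptake in only half of the PMR-only patients, (10 + 30)/80 = 50%

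Over 12 assumed mixes (40 to 70 PMR-only patients, all with uptake; TAB positive in 70–100% of cranial and 30–50% of large-vessel GCA), overall agreement is about 5–25% with PMR uptake counted and about 58–92% without. These overall figures show sensitivity to the definition. They do not predict the planned output.

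**Step 4. Agreement without association.** For unrelated tests, agreement = ab + (1 − a)(1 − b). With TAB positive in 15% and PET positive in 20%: 0.15 × 0.20 + 0.85 × 0.80 = 0.03 + 0.68 = 71%, kappa 0. Over TAB 10–30% and PET 20–30% the range is 58–74%. A PET that was never positive would agree overall in (80 − 20)/80 = 75% of patients with 20 positive biopsies and (80 − 4)/80 = 95% with 4. Its positive agreement would be zero, so reporting the two proportions separately would expose it.

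**The case against.** Study II is titled an agreement study, section 3.9 describes the secondary objectives as hypothesis-generating, and the protocol itself discloses the limits of both tests. Agreement is a legitimate description of how often they concur. All of this stands.

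Outcome 1 can also be read in other ways. If it means two separate comparisons, the vasculitis comparison is consistent with outcome 2, and the PMR comparison is left without a negative counterpart. If both findings are required, a patient with vasculitis alone falls into neither category. The text does not say which is meant, and each reading needs a correction.

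Three stronger readings are tempting but not supported:
- **One pooled agreement figure, driven by double negatives or capped by PMR uptake.** With PET positive in 75% and TAB positive in 15%, for example, agreement could not exceed 1 − (0.75 − 0.15) = 40%. Section 3.8 lists positive and negative agreement separately and defines the negative side on vasculitis alone, so such a figure may not be what is planned. The documents give no TAB or PET rates and do not say that most biopsies will be negative.
- **Study II cannot inform the question in either direction.** The number of TAB-positive, PET-negative patients bears directly on whether TAB could be dropped; many such patients would count against it.
- **The absence of kappa or confidence intervals is a fault.** An article may leave these to an analysis plan that is not shown.

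**Conclusion.** The point holds in two parts. First, the PET-positive and PET-negative definitions in section 3.8 are not complements, and sections 3.4.1 and 3.8 conflict with the Discussion. This follows from the text on the natural reading and rests on no assumed rate. Its size depends on how many patients have PMR uptake alone: 36 or 66 of 80 in the illustrations, but unknown from the documents.

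Second, agreement with TAB cannot by itself establish diagnostic validity, because by the protocol's own account the two tests examine different arteries and TAB can be falsely negative. Every case in which PET is right and TAB is wrong counts against PET. The 17% discordance with error-free reading depends wholly on the assumed case mix; the 12 mixes give about 8–42%.

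This should be corrected. It affects a secondary, exploratory objective and leaves agreement usable as a description.

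**What to change.** 1. In section 3.8, use one PET definition for the TAB comparison: large-vessel vasculitis (arterial score of 2 or more) versus none. Report PMR uptake separately, against the clinical diagnosis. Reconcile sections 3.4.1 and 3.8 with the Discussion so that PET-positive has one stated meaning for each target condition.
2. Report positive and negative agreement from that single 2×2 table, in all patients and in those with clinically suspected GCA.
3. Either restate the objective and conclusions as agreement and complementarity, or assess PET and TAB each against the one-year clinical diagnosis, recorded before the PET results are unveiled.

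The cost is wording and, for the second option in item 3, one recorded field. Restating the objective may need a formal amendment under section 3.15. The clinical reference has limits that must be disclosed. It is made with knowledge of TAB, which favours TAB. It may also not be fully blind to PET, because section 3.4.1 allows unexpected or actionable findings to be passed to the responsible physicians earlier.

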### Ethical consideration

3.13

Initial and control blood samples will be taken regarding the routine management of PMR/GCA patients. There is no further risk, for example, pain or infection for included patients compared with other patients not participating in this study. The outpatient visit may take longer time due to systematic history taking and physical examination, PWV assessment, and so on, which is a disadvantage for a busy patient.

An 18F-FDG PET/CT scan exposes a patient to about 8 mSv radiation. The average per capita background radiation is 4 mSv per year in Denmark. The average lifetime risk of cancer is approximately 25% for a 25-year-old person in Denmark. The radiation dose from one 18F-FDG PET/CT scan increases this risk to approximately 25.01%. In persons above 50 years of age, the increased risk is even less.

Due to increased rate of malignancy in PMR/GCA, patients may benefit from 18F-FDG PET/CT scan, which detects possible concurrent malignancies.

Whole-body DXA scan will be performed at baseline and a year after which is appropriate for patients receiving steroids. Evaluating fat mass takes place during the same session and extends the study by about 5 minutes which is acceptable. The radiation dose of whole-body DXA is negligible.

Vascular stiffness will be measured by SphygmoCor in conjunction with routine outpatient controls. This method is completely noninvasive and takes about 15 to 30 minutes.

Although performing 18F-FDG PET/CT scan together with TAB is a disadvantage of this study, patients are hopefully not required to do TAB in future. TAB may still be required in small number of patients.

### Research ethics approval

3.14

The present study protocol is approved by the Regional Ethics committee of the Region of Southern Denmark (identification number: S-20160098) and Danish Data Protection Agency (J.nr 16/40522). This study is also registered at clinicaltrials.gov (ClinicalTrials.gov Identifier: NCT02985424).

### Protocol amendment

3.15

Any modifications to the protocol which have substantial effects on the conduct of the study, potential benefits to the patient or impact on patient safety, including changes to eligibility criteria, patient population, sample size, study objectives, study design, study procedures, and treatment plan will require a formal amendment to the protocol. Such amendment will be sent to the Ethics committee for further approval before implementation. Administrative changes of the protocol defined as minor corrections having no effect on the way the study is to be conducted will be documented and the Ethics committee may also be notified of them.

### Consent

3.16

The PhD student is responsible for obtaining informed consent from potential participants or authorized surrogates. All participants will be informed about the voluntary nature of the participation in the study and will be received detailed information about diagnostic and treatment modalities.

### Confidentiality

3.17

The PhD student will give a unique code to each participant which will be used to identify them during the study. Any kinds of paper reports, laboratory specimens, administrative form, and so on will be identified by theses codes. All data collection sheets, patients consent forms, daily registration chart, and so on will be secured in an office with limited access. All digital files will be saved in our local databases which are password protected.

### Dissemination

3.18

The current study is a large-scale study and will form the basis of a PhD thesis. The hard copy of our work will be available at the University of Southern Denmark library once completed. The results of the study are intended for the following potential papers (preliminary titles) that will be sought published in international peer reviewed journals, or presented at International or national congresses orally.1.The clinical picture in PMR/GCA patients with and without PET detected vasculitis.2.Validity of 18FDG PET-CT scan for diagnosis of PMR/GCA compared with TAB: An agreement study.3.Prevalence of newly diagnosed malignancies in PMR/GCA patients with the aim of 18F-FDG PET/CT scan and CXR/Abdominal US: A blinded prospective study.4.Effects of steroid treatment on Bone mineral density and body composition in PMR/GCA patients: A prospective study.5.Effects of steroid treatment on vasculitis/vascular stiffness of PMR/GCA patients with the aim of PWV measurement: A prospective study.

After the completion of data collection, no later than 3 years, we will deliver a deidentified dataset to a suitable data archive for sharing purposes.

## Discussion

4

The proposed study will explore the potential role of 18F-FDG PET/CT scan in the early diagnosis and management of PMR/GCA before initiation of steroid treatment, and also the association between 18F-FDG PET/CT findings and the clinical picture of the patients. Though 18F-FDG PET/CT is not yet capable of evaluating temporal artery due to inadequate resolution, the extracranial involvement of large vessels, mainly thoracic aorta, carotid, and subclavian, can be delineated.^[53]^ Patients with positive 18F-FDG PET/CT findings will be classified as having GCA and not isolated PMR, which is of great importance in the clinic due to different steroid treatment regimes. Besides, GCA patients with aortic involvement are at increased risk of aneurysm formation, who seek close monitoring.^[54]^ It is our hope that our results elucidate the 3 main areas of concern regarding the management of PMR/GCA including: malignancy, osteoporosis/changes in body composition, the vasculitis process, and the interaction between them, and ultimately elucidate factors predictive of the disease outcome.
